# BiClamp® forcep liver transection versus clamp crushing technique for liver resection: study protocol for a randomized controlled trial

**DOI:** 10.1186/s13063-015-0722-1

**Published:** 2015-04-30

**Keywords:** Clamp crushing, BiClamp® forcep transection, Blood loss, Randomized controlled trial

## Abstract

**Background:**

Blood loss and the requirement of blood transfusions during liver transection have been shown to correlate well with higher morbidity and mortality rates and a worse prognosis. Various devices for liver parenchymal transection have been developed to reduce intraoperative blood loss. The goal of this study is to evaluate the safety and effectiveness of BiClamp® forcep transection compared to a clamp crushing technique in patients undergoing liver resection.

**Methods/Design:**

This study will include patients 18 years and older scheduled for hepatectomy with hepatic vascular exclusion who give informed consent. A sample size of 48 patients in each randomization arm will be calculated to detect a difference in the reduction of blood loss of approximately 200 ml (90% power and α = 0.05 (two-tailed)). The primary efficacy endpoint of the trial will be the total intraoperative blood loss based on the randomized dissection technique. The statistical analysis is based on the intention-to-treat population. Patients will be followed up on for three months for complications and adverse events.

**Discussion:**

This prospective, single-center, randomized controlled, single-blinded, two-group parallel trial is designed to assess the efficacy and safety of BiClamp forcep hepatectomy versus clamp crushing for parenchymal transection during elective hepatic resection.

**Trial registration:**

This trial was registered with Clinicaltrials.gov (identifier: NCT02197481) on 15 July 2014.

## Background

Minimization of blood loss during liver resection remains a major concern for hepatic surgeons due to the correlations among excessive hemorrhage, requirement of blood transfusions, higher morbidity and mortality rates and poor long-term outcomes [1-3]. In the last few decades, various techniques have been adopted to decrease intraoperative blood loss during hepatectomy, including inflow occlusion and low central venous pressures. Assuming that inflow occlusion and low central venous pressure (CVP) anesthesia cause significant damage via ischemia and reperfusion [4,5], the method applied for hepatectomy has been considered to be the most critical factor influencing intraoperative blood loss [6].

Since the clamp crushing technique was introduced in the 1980s [7], numerous high-tech equipment has been developed to improve parenchymal transection [8-10]. Randomized clinical trials and a recent meta-analysis have shown that these modern devices result in similar blood loss and transfusion requirements compared to the clamp crushing technique, but with a higher cost due cost of the device and disposable medical apparatus [6,8-10]. The optimal method for liver parenchymal division to obtain minimal blood loss is controversial. Therefore, hepatic surgeons still select the method for liver transection according to their own preferences.

Bipolar vessel sealing (BiClamp® forceps, ERBE Elektromedizin, Tübingen, Germany) is a novel hemostatic device that can seal large tissue bundles and blood vessels up to 7 mm in diameter. The BiClamp forceps resist repetitive autoclaving sterilization, which reduces health care costs and medical waste. In a randomized clinical trial, the application of BiClamp forceps significantly decreased operation time, blood loss and costs in patients undergoing mastectomy and vaginal hysterectomy [11,12]. Our retrospective analysis has provided primary evidence for BiClamp forcep efficacy and safety for liver transection [13]. However, the retrospective non-randomized design of this study could not draw a definitive conclusion. Therefore, we conduct this randomized controlled trial to verify the superiority of the BiClamp forceps during liver transection.

## Methods/Design

### Study aim

The objective of this trial is to compare two different liver transection techniques for liver resection in regards to the total intraoperative blood loss, operation time, liver transection time, intraoperative blood transfusion requirement, reoperation, hepatic injury, duration of postoperative hospital stay, total hospitalization expenditures, mortality and morbidity.

### Patient involvement

The sample size is based on a two-sided t-test for differences with respect to the primary parameter and primary analysis. In a retrospective analysis of our own series, the mean intraoperative blood loss was 450 ml those who underwent BiClamp forceps liver resection, with a standard deviation of 350 ml [14,15]. With a two-sided level of significance α = 5% and a power of 1-β = 90%, a sample size of 43 patients in each group is required to detect a difference in the reduction of blood loss of approximately 200 ml (NCSS and PASS 11 (NCSS, Utah, USA). Assuming an expected withdrawal rate of 10% during the trial, 10 additional patients will be randomized, and a total number of 96 patients need to be enrolled (Figure 1).

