#### Randomization

To achieve comparable groups in terms of known and unknown risk factors, randomization will be performed. The allocation schedule will be generated by computer-generated random numbers, with an allocation ratio of 1:1 equal probability of assignment to each group. All patients will be randomized using consecutively numbered opaque envelopes sealed by the investigators. Envelopes will be opened upon entrance of the patient to the operating room.

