## Discussion

Since the introduction of the clamp crushing technique in 1973 [7], this technique has become the gold standard for liver parenchymal transection due to its effectiveness in controlling blood loss, reduction in operative time and low cost. A variety of devices have been developed to improve parenchymal transection in the past 10 to 15 years [8-10]. However, many randomized studies have failed to show any significant advantage over the clamp crushing technique [8-10]. BiClamp forceps, a reusable bipolar sealing instrument, has been available for open surgery procedures since 2002 [11]. Our retrospective data from between July 2007 and July 2014 has shown a significant reduction in blood loss and lower costs in patients operated on using BiClamp forceps. Based on these results, the first randomized controlled trial is designed to evaluate the efficacy, safety and cost-effectiveness of BiClamp forceps compared to the clamp crushing technique during elective hepatic resection.

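### The 90% power claim rests on a blood-loss SD reported for the BiClamp series only; by the stated t-test it would need a clamp-crushing SD well below that one, despite an implied mean 200 ml higher

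*Protocol article*

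**What the plan says.** All sizing inputs are in the Patient involvement section of the protocol article.

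- Method: "The sample size is based on a two-sided t-test for differences with respect to the primary parameter and primary analysis".
- Mean and SD, from a retrospective series: "the mean intraoperative blood loss was 450 ml those who underwent BiClamp forceps liver resection, with a standard deviation of 350 ml".
- Error rates: "With a two-sided level of significance α = 5% and a power of 1-β = 90", that is, 90% power.
- Target: "to detect a difference in the reduction of blood loss of approximately 200 ml".
- Result: "a sample size of 43 patients in each group is required".
- Allowance for withdrawal: "Assuming an expected withdrawal rate of 10% during the trial, 10 additional patients will be randomized, and a total number of 96 patients". With 1:1 allocation (Randomization section), that is 48 per arm.

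No mean or SD for clamp crushing appears anywhere in the article. The abstract repeats the 90% power and 200 ml but attaches them to 48 per arm. The Discussion says of the group's own series: "Our retrospective data from between July 2007 and July 2014 has shown a significant reduction in blood loss" with BiClamp. The Statistical analysis section makes the primary test an analysis of covariance adjusting for transection area, CVP, INR and platelet count.

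**The concern.** A two-sample t-test calculation needs the variance in both arms, and the article prints it for one. The printed one belongs to the arm expected to bleed less. A 200 ml benefit over a BiClamp mean of 450 ml implies a control mean of about 650 ml, which is never written. Blood loss cannot be negative and the printed SD is 78% of its mean, so a wider spread in the heavier-bleeding arm is plausible.

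The SD determines what a non-significant primary result can mean. With 90% power, a null result would count fairly strongly against a 200 ml benefit. With power nearer 79%, or lower, it would count for less, and a reader of the abstract could not tell.

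This is an input problem. The printed 43 per arm also fails to follow from an SD of 350 ml in both arms, but correcting that arithmetic alone would leave the control SD unstated.

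**Working it through.** **Inputs from the article:** difference 200 ml; BiClamp mean 450 ml, SD 350 ml; two-sided α 0.05; power 90%; 43 per arm before and 48 per arm after the withdrawal allowance. **Assumed:** the control SD.

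**1. The plan's own figure.** With SD 350 ml in both arms,

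n per arm = 2 × (1.960 + 1.282)² × 350² / 200² ≈ 64.4, so 65 by the normal approximation and 66 by the exact noncentral t.

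The printed 43 is not reproduced. Two-sided 80% power gives 49 to 50, one-sided 90% gives 53 to 54, and one-sided 80% gives 38 to 39. Obtaining 43 would take, for example, a common SD of about 281 ml or a difference of about 249 ml. The article states neither. The step from 43 to 48 is correct: 43 / 0.9 = 47.8.

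**2. The control SD that 90% power needs.** With unequal SDs,

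SE = √[(350² + SD_control²) / n], noncentrality = 200 / SE, Welch degrees of freedom.

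Solving for 90% power gives SD_control ≈ 191 ml at n = 43 and ≈ 237 ml at n = 48. Against an implied control mean of 650 ml these are coefficients of variation of 191/650 = 0.29 and 237/650 = 0.36. The BiClamp series has 350/450 = 0.78.

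**3. Power for 200 ml over a range of assumed control SDs.** The value 506 ml keeps the BiClamp coefficient of variation: 650 × 350/450 = 505.6. The value 428 ml is midway between 350 and 506.

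| Assumed control SD (ml) | Power, 43 per arm | Power, 48 per arm | Difference detectable with 90% power, 48 per arm |
|---|---|---|---|
| 300 | 80% | 85% | 218 ml |
| 350 | 75% | 79% | 234 ml |
| 428 | 65% | 70% | 261 ml |
| 506 | 56% | 60% | 291 ml |

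Example, SD 350 and n = 48: SE = √[(350² + 350²)/48] = 71.4, noncentrality = 200/71.4 = 2.80, critical t = 1.99 on 94 degrees of freedom, power 0.79.

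**4. Skewness.** Simulated lognormal data analysed by the t-test gave similar values at 48 per arm: 79% with control SD 350 ml and 64% with 506 ml.

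**5. Covariance adjustment.** If the covariates explain a share R² of the variance, both SDs shrink by √(1 − R²). At 48 per arm with SD 350 ml in both arms, power is about 87% at R² = 0.20 and 91% at R² = 0.30. With a control SD of 506 ml, the SD increase alone is offset at R² = 1 − 350² / [(350² + 506²)/2] ≈ 0.35, which restores about 79%. Reaching 90% would take about 1 − (200/291)² = 0.53. The article states no R².

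**The case against.** Four objections have weight.

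First, a reader might infer that 350 ml was entered as the common SD. The article does not say so, and its own number speaks against it, because 350 ml in both arms needs 65 to 66 patients per arm rather than 43. What stands is that the SD used for the control arm is undisclosed.

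Second, a reader might infer that the control SD must exceed 350 ml, so that 79% is a ceiling. The article gives no control SD. A value below 350 ml would raise the power: 300 ml gives about 85% at 48 per arm and 250 ml about 89%. The trial also fixes one surgeon, low CVP and a standard Pringle schedule (Standardization of perioperative care), which could narrow the spread compared with a retrospective series. A constant coefficient of variation is a reasonable heuristic, not a fact from the document. Even so, 250 ml still falls short of 90%.

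Third, a reader might infer that the primary analysis itself is underpowered. That does not follow, because it is a covariance analysis and the covariates could recover power (step 5). But the sizing is presented as a t-test and claims no variance reduction, so the printed 90% cannot be defended on that ground as it stands.

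Fourth, the article may be condensing a fuller protocol, and the references given for the 450/350 ml figures differ from the one given for the retrospective analysis in the Background. It is therefore likely, but not certain, that matching control figures are at hand. This tempers the fix. It does not remove the point, because the article does print a power claim together with inputs that do not support it.

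**Conclusion.** The point holds in a limited form. The 90% power claim rests on an SD given for one arm, the arm expected to bleed less. By the stated t-test it is not met for any control SD at or above the only SD printed. Meeting it would need a control SD of about 191 ml (43 per arm) or 237 ml (48 per arm), which is implausible beside a control mean about 200 ml higher. With 350 ml in both arms, power at 48 per arm is about 79%.

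The range of about 85% to 60% is conditional on an assumed control SD of 300 to 506 ml, on the implied control mean of 650 ml, and on an unadjusted comparison. The document does not establish that the true power is at the low end, nor that the planned adjusted analysis falls short. The sponsor should correct this, because readers will rely on the power figure when interpreting a null result.

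**What to change.** In Patient involvement, state the mean and SD used for each arm, taking the clamp-crushing figures from the retrospective comparison if they are available. With those two SDs, restate either the power for 200 ml or the difference detectable with 90% power, at the planned 48 per arm. With 350 ml in both arms that is about 79% power, or about 234 ml.

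If the control SD cannot be recovered, print a range and label it as an assumption: for control SDs of 300 to 506 ml, about 85% to 60% power, or about 218 to 291 ml detectable.

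Label these as unadjusted t-test figures. Claim a gain from the covariance analysis only with a stated R² and its source. Carry the restated figure into the abstract, which now attaches 90% to 48 per arm.

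The cost is a few sentences and a rerun of the calculation. No extra patients are needed and no endpoint or analysis changes, but the stated power becomes less favourable.

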## Trial status

The study protocol has been completed in July 2014. Enrollment started on 1 October 2014. [name] performs approximately 80 hepatectomies per year. The estimated time frame to randomize 48 patients will be approximately 20 months.

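### The 43 patients per group give about 75% power, not 90%, on the protocol's own inputs (200 ml, SD 350 ml, two-sided 5% t-test)

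*Protocol article*

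**What the plan says.** All the inputs stand in the Patient involvement section of the protocol article.

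- Test: "The sample size is based on a two-sided t-test for differences with respect to the primary parameter and primary analysis".
- Error rates: "With a two-sided level of significance α = 5% and a power of 1-β = 90"%.
- Effect: "to detect a difference in the reduction of blood loss of approximately 200 ml".
- Variability: the BiClamp patients in the centre's own retrospective series had a mean blood loss of 450 ml, "with a standard deviation of 350 ml". No SD or mean is given for clamp crushing.
- Result: "a sample size of 43 patients in each group is required to detect a difference in the reduction of blood loss". Ten patients are then added for 10% withdrawal, making 96 in total.

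The abstract attaches the same power and difference to the inflated number: "A sample size of 48 patients in each randomization arm will be calculated to detect a difference in the reduction of blood loss". The Trial status section says: "The estimated time frame to randomize 48 patients will be approximately 20 months".

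**The concern.** The standardised difference is 200/350 = 0.57, a moderate effect. A two-sided 5% comparison with 90% power at that effect size takes well over 60 patients per group, so 43 looks too small at once.

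Total intraoperative blood loss is the only primary endpoint, and the Background gives the trial's purpose as verifying superiority. Both the Background and the Discussion report that earlier devices failed to beat clamp crushing. Against that history, a non-significant result backed by a claim of 90% power could be taken as firm evidence against a 200 ml benefit, when the design as calculated would miss such a benefit more than twice as often as stated.

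**Working it through.** **Inputs.** Difference Δ = 200 ml; SD σ = 350 ml, taken as common to both arms because it is the only SD given; two-sided α = 0.05; power 0.90 (all from Patient involvement); 1:1 allocation (Randomization).

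**1. Sample size for 90% power.** The normal approximation is

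n per group = 2(z₀.₉₇₅ + z₀.₉₀)² (σ/Δ)² = 2 × (1.960 + 1.282)² × (350/200)² = 2 × 10.51 × 3.0625 = 64.4, so 65.

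The exact noncentral-t calculation gives 65.3, so 66 (power 0.8985 at 65 and 0.903 at 66). The stated 43 is not reproduced.

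**2. Power at the planned sizes.** The normal approximation is power = Φ(Δ/(σ√(2/n)) − 1.960).

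- n = 43: 200/(350 × 0.2157) = 2.650; Φ(0.690) = 0.755. Exact t: 0.745.
- n = 48: 200/(350 × 0.2041) = 2.799; Φ(0.839) = 0.799. Exact t: 0.791.

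**3. The withdrawal step.** 2 × 43 = 86, and 86/0.9 = 95.6, so 96. This step is right. The fault lies in the 43 or in its inputs.

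**4. Search for a variant that gives 43** (exact t unless noted; Δ = 200 and σ = 350 unless stated).

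| Variant | n needed |
|---|---|
| Two-sided 5%, 90% power (as stated) | 66 per group |
| One-sided 5%, 90% power | 54 per group |
| Two-sided 5%, 80% power | 50 per group |
| One-sided 5%, 80% power | 39 per group |
| Paired or one-sample, 90% power | 35 |
| Mann-Whitney (inflation by π/3), 90% power | about 69 per group |
| Δ = 220 ml, two-sided, 90% power | 55 per group |

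None gives 43.

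**5. What would have to be true for 90% power.**

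- Standardised difference: 0.707 at n = 43 and 0.669 at n = 48.
- With σ = 350: Δ = 247.5 ml (n = 43) or 234.0 ml (n = 48).
- With Δ = 200: common SD = 282.8 ml (n = 43) or 299.2 ml (n = 48).
- With 350 ml in the BiClamp arm only, n = 43: the control SD would have to be √(2 × 282.8² − 350²) ≈ 194 ml.
- Through covariate adjustment: R² = 1 − (282.8/350)² = 0.347 (n = 43) or 1 − (299.2/350)² = 0.269 (n = 48).

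**6. Sensitivity to the unstated control SD** (an assumption; BiClamp SD held at 350 ml).

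| Control SD | Power, n = 43 | Power, n = 48 |
|---|---|---|
| 250 ml | 85% | 89% |
| 300 ml | 80% | 84% |
| 350 ml | 75% | 79% |
| 400 ml | 68% | 73% |
| 505 ml (SD proportional to a 650 ml mean) | 56% | 61% |

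**7. Trial status.** 80 hepatectomies a year for 20 months is 80 × 20/12 = 133. Recruiting 96 would take 72% of them, and 48 would take 36%. Read literally, the 48 patients conflict with the total of 96. It may be a per-arm figure, but the text does not say so.

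**The case against.** The arithmetic itself is not in dispute. The best arguments on the other side concern what it implies.

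- **The common SD is an assumption.** The 350 ml belongs to the BiClamp series, so 43 may reflect an unreported input and not a slip. That is possible, but it would need a control SD of about 194 ml. The article offers no such figure, and it would give the smaller spread to the arm expected to bleed more. As written, the inputs still do not yield the result.
- **The primary analysis is an ANCOVA**, adjusting for transection area, CVP, INR and platelet count (Statistical analysis). This has substance. With assumed R² of 0.10, 0.20 and 0.30, power is 79%, 83% and 88% at 43 per group, and 83%, 87% and 91% at 48. So 75–79% is the power of the t-test on which the sample size was based, and the power of the planned analysis is unknown. But the calculation names a t-test and claims no gain from covariates, so the 90% cannot be credited to adjustment.
- **48 is the more realistic number.** Envelopes are opened on entry to the operating room, the endpoint is complete at skin closure, and analysis is by intention to treat, so few primary outcomes should be lost. This is fair, and it moves the figure to 79%, still short of 90%.
- **The 505 ml scenario is speculative.** Agreed. It is one end of an assumed range, and nothing here depends on it.
- **The 48 in Trial status is probably per arm.** That is plausible. It is a wording point with no bearing on the power.

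**Conclusion.** The concern holds. With SD 350 ml in both arms, a 200 ml difference and a two-sided 5% t-test, 90% power needs 66 per group. The planned 43 gives 74.5%, and 48 gives 79.1%. The type II error is 21–25% instead of 10%, and the difference detectable with 90% power is about 248 ml (43 per group) or 234 ml (48 per group). The statement is wrong in both Patient involvement and the abstract.

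The result rests on one assumption, that the only SD given applies to both arms, and it describes the unadjusted comparison the calculation names. Adjustment could bring the power back to 90%, but only with an R² of about 0.35 (43 per group) or 0.27 (48 per group), which the article does not assume. Because this is the stated power for the sole primary endpoint, it should be corrected.

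**What to change.** 1. Retrieve the inputs given to the sample-size software. If another SD, a separate control-arm SD, another difference or a covariate R² was used, state it with its source, so that 43 can be reproduced.
2. If there was no such input, keep 96 patients and correct the power in Patient involvement and the abstract. Suggested wording: 43 evaluable patients per group give about 75% power, and 48 per group about 79%, to detect 200 ml with an SD of 350 ml in a two-sided 5% t-test; 90% power applies to a difference of about 248 ml (43 per group) or 234 ml (48 per group).
3. In Trial status, say whether the 20-month projection is for 96 patients in total or 48 per arm.

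This costs wording only, with no extra patients, though the stated power becomes less favourable. Should the sponsor want a true 90% on the stated inputs, that takes 2 × 66 = 132 evaluable patients, or 132/0.9 = 146.7, so 147 enrolled. That is 51 more than planned, and the correction does not require it.

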**Figure 1 Fig1:**
[figure not shown]
Flowchart according to CONSORT (Figure 1).

### Eligibility criteria

#### Inclusion criteria

Patients who meet the following criteria will be included in the study:Above 18 years of age,Elective hepatic resection due to benign or malignant hepatobiliary disease,Child-Pugh class A or B liver function andInformed consent.

#### Exclusion criteria

Patients who meet any of the following criteria will be excluded from the study:Participation in concurrent intervention trials with interference in the outcome of this study,Laparoscopic hepatectomy,Preoperative liver function evaluation: Child-Pugh class C,Lack of compliance orPregnancy or lactation.

#### Withdrawal

Patients can withdraw at their own request or at the legal representative’s request at any time during the trial. Patients may also be withdrawn if, in the investigator’s opinion, continuation of the trial may be detrimental to the patient’s wellbeing. The reason for all withdrawals will be recorded in the clinical report forms (CRFs) and in the patient’s medical records. All data will be analyzed according to the intention-to-treat (ITT) principle [16].

